#### Analysis of the patient satisfaction with the telemonitoring procedure

The validity and reliability of the patient satisfaction questionnaire will be analysed. A panel of experts in Health Technology Assessment will evaluate the face and content validity of the instrument. Cronbach alpha will be calculated to measure the reliability of each scale. An exploratory factor analysis will be conducted to determine the construct validity. Convergent and divergent validity of the items will be assessed by determining the correlation between each item and the factors.

The scales corresponding to each of the domains of the questionnaire will be calculated by summing up the responses obtained for all items on that scale and will be standardised on a 0 to 100 scale. Given the absence of a gold standard, the criterion-related validity will be studied by determining whether the patients reporting lower levels of satisfaction correlate with higher mortality rates, longer hospital stays, higher number of hospital admissions, higher use of health care resources and more episodes of worsening. In addition, the scales of the questionnaire will be compared by socio-demographic and baseline clinical characteristics. The Student t-test or the analysis of variance will be used for normally distributed data, and the Mann Whitney U test or the Kruskal-Wallis test for non-normally distributed data.

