#### Outcome measures

All the outcome measures will be collected after 3, 6 and 12 months of follow-up, except for satisfaction with the telemonitoring technology, which will be measured only once (approximately after 3 months from the start of the study). Table 2 shows a summary of the outcome variables that will be evaluated in the present study.

**Table 2 T2:** Summary of the outcome measures analysed in the study.

	Primary outcome measure	Secondary outcome measures
**Mortality**		- Mortality due to any cause
		- Mortality due to HF or CLD
		
**Use of health care resources**	- Hospital admissions due to any cause	**- **Hospital admissions due to HF or CLD
		- Duration of hospital stay
		- Emergency department visits
		- Home visits by GP or nurses
		- Visits to primary care centres by family or caregivers
		- Telephone contacts with professionals
		- Visits to specialist doctors
		
**Clinical efficacy**		- Worsening of the patients' pulmonary and/or heart condition (number of episodes)
		
**Functional status and quality of life**		- Patient Quality of Life (EQ-5D questionnaire)
		- Functional status (Barthel Index)
		- Caregiver burden (Zarit Burden Interview)
		
**Cost-effectiveness**		- Cost-effectiveness (using QALYs)
		
**Satisfaction with the new technology**		- Degree of satisfaction of patients and health care professionals
		
**Compliance**		- Patient and provider compliance with the telemonitoring

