2.7 *Other variables of clinical efficacy: number of episodes of worsening of the pulmonary and/or heart condition*. An episode of worsening or exacerbation is defined as a sustained worsening of the patient's symptoms from a usual stable state that is beyond normal day-to-day variations and is acute in onset. Commonly reported symptoms are oedema, breathlessness and nocturia for HF, and worsening breathlessness, cough, increased sputum production and change in sputum colour for CLD. An episode of worsening is considered a change in these symptoms that requires intervention or control by the physician.

2.8 *Functional status*. The Barthel Index (BI) [22] will be used to measure Activities of Daily Living (ADL). The score on the BI ranges between 0 and 100, with results indicating: total dependence (0-20), severe dependence (21-60), moderate dependence (61-90), little dependence (91-99), and total independence (100).

2.9 *Caregiver burden*. The burden of the family/caregiver will be measured using a validated Spanish version of the Zarit Burden Interview (ZBI) [26-28]. The score ranges from 0 (no burden) to 88 (highest level of burden).

2.10 *Degree of acceptance and satisfaction of patients and health professionals*. The degree of satisfaction of the patients with the telemonitoring intervention will be assessed using a questionnaire based on validated published surveys adapted for this study [29-31]. It consists of 18 items grouped in eight dimensions. The patient satisfaction questionnaires will be administered at the patient's home by an independent female sociologist not involved in the care process. The degree of satisfaction of GPs and nurses participating in the intervention group will be assessed through a qualitative study based on focus group methodology and by means of a specific questionnaire designed *ad hoc*. A Web-based version of the questionnaire for health care professionals will be delivered electronically.

2.11 *Evaluation of the technical performance and compliance with the telemonitoring system*.

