### Sample size

Thirty patients will be recruited in each of the study groups, the main constraints being the number of available devices and the number of potential patients fulfilling the inclusion criteria in the Bilbao Primary Care Health Region. Thus, if 30 patients are included in each group, and a 10% loss to follow-up is assumed at 12 months (based on previous analysis of mortality and other causes of loss in patients with similar characteristics), we have estimated a statistical power of 72% to detect significant differences between the CG and the IG in the mean number of total admissions with a level of significance of 5%. For the power calculation, it has been assumed that the mean number of admissions in the CG is 3.5, the standard deviation 1.7, and there will be a 35% decrease of hospitalisations in the IG with respect to the CG [32-34]. The power calculations have been performed with the sample size calculation software Ene 2.0.

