### Study limitations

Due to the interactive nature of the intervention, it is not possible to blind the health care professionals providing the intervention or the participants involved in the study. Despite the aforementioned limitation, most of the key data are objective and will be obtained from medical registers (hospital admissions, use of health care resources, etc.). Methods have been put in place to double-check the veracity of the data obtained. Moreover, the statisticians in charge of the data analysis will be blinded to group assignment.

The number of patients included in the present study is limited by the available telemonitoring devices. Despite recruitment of a higher number of patients would have been desirable, we have estimated a power of 72% to detect significant differences in the main outcome measure between the two study groups.

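### With at most 30 respondents, a factor analysis of the 18 satisfaction items cannot determine an eight-dimension structure, so it should not support a claim of construct validity

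*Protocol article*

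**What the plan says.** Secondary outcome 2.10 describes the instrument as a survey of patients' satisfaction with telemonitoring, adapted for this study from validated published surveys: "It consists of 18 items grouped in eight dimensions". The Outcome measures section sets satisfaction apart from the 3-, 6- and 12-month schedule, as something "which will be measured only once (approximately after 3 months from the start of the study".

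The section on analysis of patient satisfaction plans five things:

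- an expert panel for face and content validity;
- Cronbach alpha for each scale;
- a factor analysis: "An exploratory factor analysis will be conducted to determine the construct validity";
- convergent and divergent validity, from the correlation of each item with the factors;
- criterion validity, from whether "patients reporting lower levels of satisfaction correlate with higher mortality rates", and likewise with longer stays, more admissions, more resource use and more worsening episodes.

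Scale scores are sums over the items of each questionnaire domain, rescaled to 0 to 100.

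On numbers, the Sample size section states: "Thirty patients will be recruited in each of the study groups". Study limitations adds: "The number of patients included in the present study is limited by the available telemonitoring devices". That section discusses the small sample only for the main outcome.

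**The concern.** The factor analysis is given the job of determining construct validity, and the item-factor correlations the job of showing convergent and divergent validity. Both need a stable correlation matrix. Here the matrix would come from one survey of a group that cannot grow, because devices are limited. The factors are fitted to the same answers they are then correlated with, so those correlations are high partly by construction.

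At stake is a claim, not the trial's main result. Satisfaction is a listed secondary outcome and the subject of the third secondary objective. Followed as written, the plan ends in a statement that the questionnaire's construct and criterion validity were shown, or were not, from data that can support neither.

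**Working it through.** **Inputs.** From the protocol article: 18 items and 8 dimensions (outcome 2.10), 30 patients per group (Sample size), one survey at about 3 months (Outcome measures), and "a 10% loss to follow-up is assumed at 12 months" (Sample size). That only intervention patients answer is an inference from what the questionnaire rates. The article gives no retention rule or rotation, so those used below are assumptions.

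**The plan's own figure.** There is none for this analysis. The stated 72% power concerns admissions. With a difference of 0.35 × 3.5 = 1.225, SD 1.7, 27 per group and a two-sided 5% level, the noncentral t gives 73.8%, which agrees closely. Nothing below depends on it.

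**Information available.**
- Respondents: at most 30. Applying the 12-month loss gives 30 × 0.9 = 27. The survey comes earlier, so 27 to 30 is a fair range, before any non-response.
- Respondents per item: 30/18 = 1.7, or 27/18 = 1.5.
- Correlations to estimate: 18 × 17/2 = 153.
- Items per dimension: 18/8 = 2.25, so mostly two-item scales.

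**Noise compared with structure.** Eighteen items were simulated and correlation-matrix eigenvalues above 1 were counted (3,000 runs per n for noise, 1,000 per structured case).

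| True structure | Mean factors retained, n = 27 to 30 | Exactly eight retained |
|---|---|---|
| None (uncorrelated items) | 7.55 to 7.64 | 50% to 56% |
| One factor, loading 0.7 | 3.4 to 3.7 | 0% |
| Three factors, loading 0.7 | 4.6 to 4.8 | 0% |
| Eight factors, loading 0.7 | 6.8 | 8% to 10% |

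Under this rule a real eight-factor structure yields eight factors less often than no structure does.

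**Item-factor correlations.** With uncorrelated items at n = 27 and an eight-component varimax solution (2,000 runs), the mean highest loading per item was 0.73. In an unlimited sample of uncorrelated items each component explains 1/18 of the variance, so 7.55 components would explain 7.55/18 = 42%. The retained noise components in these small samples explain about 75%. The excess is fit to chance.

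**Cronbach alpha.** For alpha 0.70, k = 2 and n = 30, the Feldt interval is 1 − (1 − 0.70) × F, with F on 29 and 29 degrees of freedom. The quantiles are 2.10 and 0.476, giving 1 − 0.30 × 2.10 = 0.37 and 1 − 0.30 × 0.476 = 0.86. At n = 27 it is 0.34 to 0.86.

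**Correlation with outcomes.** For a true r = 0.3 at n = 30 (Fisher z), atanh(0.3) × √27 = 0.3095 × 5.196 = 1.61, so power = Φ(1.61 − 1.96) = 36%. At n = 27 it is 33%.

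**Deaths.** A 10% loss from all causes, deaths included, is 3 of 30 patients. The mortality correlation would rest on three deaths or fewer, and anyone who died before the survey has no score.

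**The case against.** A reader might infer something stronger: that noise gives about eight factors, so the eight dimensions would appear confirmed whatever the data. The documents do not support that.

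- The article names no retention rule. The count near eight belongs to the eigenvalue-above-1 rule; under parallel analysis, noise factors would be retained in only about 5% of samples. An article may leave that rule to the full protocol, so its absence is not a fault.
- The article does not say that a count of eight would confirm the dimensions.
- The count does vary with the data, as the table shows.
- Noise does not reproduce the instrument. The full item grouping was recovered in 0 of 2,000 runs and mean alpha was −0.08, so the planned alpha would expose pure noise.
- The count is not a small-sample effect. Noise gives 8.05 factors at n = 60, 8.3 at n = 100 and 8.8 at n = 1,000. High loadings are likewise partly a result of extracting eight components from 18 items.

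Nor can one infer that scale scores would be built on an unstable factor solution, since the plan scores by the questionnaire's own domains. The expert panel is a sound element that does not depend on sample size. Mortality is only one of several correlates, used because no gold standard exists; whether it is suitable is partly a matter of preference.

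All of this stands, and it limits the point. It does not rescue the use of the factor analysis to determine construct validity in 30 patients.

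**Conclusion.** The point holds in a limited form. With 1.7 respondents per item at best, the factor analysis is uninformative about an eight-dimension structure, and item-factor correlations from the same patients are inflated (about 0.73 on noise at n = 27). Alpha and the outcome correlations can be reported but are too imprecise to establish validity: 0.37 to 0.86 around an alpha of 0.70 on a two-item scale, and 36% power for r = 0.3.

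This rests on two assumptions: that only intervention patients are surveyed, and that the factors and the item-factor correlations come from the same patients. The factor counts also assume the eigenvalue rule, but the conclusion does not need them. The weight is low: this is a secondary, one-arm analysis of an instrument, with no bearing on the between-group comparisons or the economic analysis.

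**What to change.** In the section on analysis of patient satisfaction:

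- Drop the factor analysis and the item-factor correlations, or label them descriptive only.
- Keep the expert panel and the domain-based scale scores as planned.
- Report Cronbach alpha for each scale with its 95% confidence interval.
- Describe associations of satisfaction with admissions, stay, resource use, worsening and mortality as exploratory.
- State that no claim of construct or criterion validity will be made from this trial.

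The change is to wording only and needs no new data. The cost is giving up the claim to have validated the questionnaire.

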#### Analysis of the technical performance and compliance with the telemonitoring system

Data concerning patient and health care professional compliance with telemonitoring, as well as the reliability, performance and security of the telemonitoring procedure over the course of the study will be described.

### Ethics approval

The study was approved by the Ethics Committee for Scientific Research (CEIC, Basurto Hospital, Bizkaia) on the 16^th ^of December 2009. Patients or relatives gave written informed consent prior to participating in the study.

### Study limitations

Due to the interactive nature of the intervention, it is not possible to blind the health care professionals providing the intervention or the participants involved in the study. Despite the aforementioned limitation, most of the key data are objective and will be obtained from medical registers (hospital admissions, use of health care resources, etc.). Methods have been put in place to double-check the veracity of the data obtained. Moreover, the statisticians in charge of the data analysis will be blinded to group assignment.

The number of patients included in the present study is limited by the available telemonitoring devices. Despite recruitment of a higher number of patients would have been desirable, we have estimated a power of 72% to detect significant differences in the main outcome measure between the two study groups.

## Discussion

The results of this study will shed some light on the effects of telemonitoring for the follow-up and management of chronic patients from a primary care setting. The present investigation will provide data on the clinical efficacy, patient's quality of life and health services costs. The level of acceptance, obstacles and facilitating factors for the use of the new telemonitoring technology will also be explored. Improving the medical support provided to elderly chronic patients and their family/caregivers has the potential to decrease health service usage and increase their quality of life through improved worsening symptom identification and a better continuity of care.

Among the main contributions of the present study we could highlight the following:

1. The telemonitoring intervention will be controlled and managed by the primary health care professionals (GPs and nurses) who routinely see the patients in the health centres. This is a realistic approach that integrates a new health care strategy within the primary health care sector. The study involves all the primary health centres in the Bilbao Health Region and, therefore, the application of ICTs to the management of chronic patients may have a significant impact on the internal organisation of an entire Health Region.

2. The subgroup of patients selected for the study suffers from two of the most commonly targeted diseases for home telecare interventions (*i.e*., HF and CLD). In addition, the patients included in the present study show certain added peculiarities: they are home care patients with frequent hospital admissions and with a higher mean age than that targeted by most other published studies. Therefore, the study may contribute to enhance the understanding of alternative modes of health care provision for medically unstable patients with a high degree of physical and functional deterioration.

3. The present study will also evaluate the acceptance of the new technology by health care professionals and patients/caregivers which could be critical for the adoption of ICTs in the health care sector. In particular, we would like to point out the considerable number of health care professionals that will be involved in the study, which could provide substantial data to thoroughly assess provider satisfaction with telemonitoring technology by means of qualitative and quantitative methods.

4. The study could provide evidence to determine the feasibility of the use of ICT applications by elderly patients with limited computer literacy.
